## Abstract

**Background:**

Despite documented effectiveness, the public health impact of vaccinations is severely limited by misperceptions, hesitancy, and poor acceptance. Messaging from health care providers has not yet been optimized to overcome these barriers and has not been tailored to groups that face health disparities, such as rural Americans. Because vaccines have become controversial, as illustrated by the public response to the SARS-CoV-2 vaccines, traditional approaches that use persuasive education or advice to change perspectives are unlikely to have long-term effects and may even be counterproductive. Alternatively, motivational interviewing (MI) is a conversational approach to address modifiable behavior and its empathic nature can be useful when navigating challenging topics. Although MI has been found to be efficacious in improving vaccination rates among children and adolescents, it is unknown whether MI can reduce vaccine hesitancy and health disparities among underserved rural adults. Further, the ideal mode of delivery for MI is unknown, especially “dose,” “intensity,” and integration with mobile health (mHealth). Therefore, it is essential to investigate the efficacy of MI in promoting vaccine uptake in rural populations to reduce health disparities.

**Objective:**

This study aims to develop and evaluate the feasibility, acceptability, and preliminary efficacy of our mHealth-based MI intervention to diminish SARS-CoV-2 vaccine hesitancy (MOTIVACC).

**Methods:**

This pilot study uses mixed methods. A 2-phase study will be conducted: convening a community advisory panel to understand barriers and facilitators to vaccination and mHealth uptake among adults (phase 1, n=16-20), and a pilot 3-group single-blind randomized controlled trial (RCT) for 8 weeks (phase 2, N=60). In the RCT, we recruit adults who have received no previous dose of the COVID-19 vaccine and randomize them into one of three arms: standard MI (SMI; n=20), intensive MI (IMI; n=20), or mHealth-based MOTIVACC (n=20). The primary RCT outcomes are positive change in vaccine hesitancy and intention to obtain the vaccines, measured on Likert scales. The secondary RCT outcome is the actual vaccine receipt.

**Results:**

Phase 1 of this study was approved by the ethics committees of both the University of Oklahoma and Oklahoma State University in July 2022, and was completed in June 2023. Phase 2 of this study was approved by the ethics committee at the University of Oklahoma in April 2024.

**Conclusions:**

This randomized trial will evaluate the preliminary efficacy of MI for targeting SARS-CoV-2 vaccine hesitancy, as well as compare traditional MI versus mHealth-based MI. This will provide pivotal data on scalable strategies to assist in navigating vaccine hesitancy, including in rural populations.

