#### Procedure

RCT participants (N=60) are randomized to one of the 3 treatment groups using simple randomization in the REDCap (Research Electronic Data Capture; Vanderbilt University) program [33,34]. These groups include standard MI (SMI; n=20), intensive MI (IMI; n=20), or mHealth-based MOTIVACC (n=20). SMI consists of one MI session at least 20 minutes in length [35-38] delivered by a trained counselor at the baseline and provision of printed self-help materials. IMI consists of the SMI component plus 3 additional MI sessions delivered by a trained counselor via telephone or video calls at weeks 2, 4, and 6 post enrollment. MOTIVACC consists of an empathy-driven, fully automated, smartphone-based MI program that involves proactive, interactive, and individually tailored messages, plus some embedded images or videos, delivered by our Insight app [39]. MOTIVACC will begin immediately after enrollment and data collection and continue for an 8-week period (about 2-5 messages or questions per day, depending on participants’ interaction and responses). The intervention content in all groups is adapted from the team’s previous work and existing empirical evidence for in-person MI [25], is informed by Phase 1 outcomes, and is designed to tap SCT mechanisms. Insight for Android is used and any participants enrolled in MOTIVACC who do not have an Android phone will be loaned one for the duration of the study. All participants are followed up at week 8 post enrollment via individualized REDCap survey links sent via email [33,34].

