### Statistical Analysis

This pilot study was designed to test feasibility, acceptability, and preliminary efficacy; thus, existing recommendations regarding sample sizes for pilot studies were used [30] versus a formal power calculation. Descriptive statistics will be used to assess the feasibility and acceptability of MOTIVACC, including the proportion of individuals who met inclusion criteria, the proportion of eligible participants who agreed to participate, the proportion of prescheduled events (intervention messages and interactive open-ended questions) delivered, viewed, or completed, and attrition rate at 8-week follow-up. The preliminary efficacy of IMI or MOTIVACC vs. SMI in changing participants’ vaccine hesitancy and uptake intention will be evaluated using generalized linear mixed models, controlling for selected covariates such as sex and education level. Secondary outcomes will be examined using log-binomial regression with an intent-to-treat approach (ie, missing=no vaccine receipt) to compare the effect of IMI or MOTIVACC on the dichotomous 1st-dose vaccine receipt outcome at 8 weeks post enrollment. As aforementioned, given the preliminary nature of the RCT, we do not expect to have sufficient power for full hypothesis testing. For missing data, we will consider a multiple imputation approach based on participants’ demographics at baseline to account for potential missing-at-random mechanisms. We also will explore pattern-mixture and selection models to account for potential (and likely) missing-not-at-random mechanisms [51].

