## Discussion

### Anticipated Findings

The results of this study will provide critical data regarding the utility of MI and MI-based mHealth interventions in targeting vaccine-related hesitancy and intention. Despite documented effectiveness, the public health impact of vaccinations is severely limited by misperceptions, hesitancy, and poor acceptance [52]. Messaging from health care providers has not yet been optimized to overcome these barriers [53-55] and has not been tailored to groups that face health disparities, such as rural Americans. Understanding the utility of different communication strategies, including those rooted in empathy, is important to navigate conversations surrounding SARS-CoV-2 vaccines, and others, as alternatives to education or advice. Motivational interviewing is a logical candidate given it is thoroughly operationalized and clearly defined, though questions regarding dose, intensity, and scalability remain. It is essential to investigate the efficacy of MI in promoting vaccine uptake in rural populations to reduce health disparities. Our study will address this need and will contribute to filling the gap in evidence regarding the dose and intensity at which MI can be (cost-) effective. While an app-based mHealth intervention does not allow for two-way or interpersonal communication (a hallmark of MI), careful design of mHealth messages, as well as the ability to share input (eg, “Share your thoughts with us”) could prove sufficient. Conversely, the use of mHealth could help alleviate common concerns that exist in MI-based studies (eg, drift in provider skills), which can be addressed via ongoing evaluation, but this is not overly scalable.

This project will be one of the first to test the use of MI, including via mHealth, to address vaccine hesitancy in adults residing in primarily rural areas. MI has long been acknowledged as a key candidate in helping to navigate difficult conversations, including conversations around general vaccine hesitancy. Although MI’s efficacy has been demonstrated in parents to vaccinate their children, its efficacy among adults, particularly rural ones, to receive vaccines for themselves is unknown. Given the convoluted nature of vaccine hesitancy secondary to the COVID-19 pandemic, autonomy-supportive and empathetic intervention strategies are essential, thus it is critical to evaluate the use of MI in this context.

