### Conclusion

Results from this pilot project will be critical for future robust fully-powered clinical trials to examine the efficacy of different MI approaches in promoting vaccination. If MOTIVACC is found to be acceptable and effective, it could be an affordable and scalable stand-alone MI intervention that can be easily and widely implemented with minimal human involvement to reduce the disease in rural populations. The long-term goal of our research is to establish a scalable, automatic, interactive, mHealth-based MI intervention that can be tailored to individuals or groups to decrease vaccine hesitancy for any type of vaccine (not just SARS-CoV-2 vaccine) and increase vaccination rates. Therefore, if successful, MOTIVACC may be adapted to be used in reducing vaccine hesitancy and promoting the uptake of other vaccines. Therefore, this study, together with our subsequent course of research, will help to reduce vaccine-preventable morbidity and mortality in rural populations.

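### Every arm receives motivational interviewing, so randomisation identifies differences between formats of MI and not the efficacy of MI that the abstract and discussion promise

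*Protocol article*

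**What the plan says.** The Procedure section of Phase 2 in the protocol article defines three groups of 20. For the reference group, "SMI consists of one MI session at least 20 minutes in length", together with printed self-help material. For the second, "IMI consists of the SMI component plus 3 additional MI sessions delivered by a trained counselor". For the third, "MOTIVACC consists of an empathy-driven, fully automated, smartphone-based MI program", which runs for 8 weeks. No untreated, usual-care, education or attention-control group is described.

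The Statistical Analysis section names the efficacy contrasts for hesitancy and intention as "The preliminary efficacy of IMI or MOTIVACC vs. SMI", fitted with generalized linear mixed models. Vaccine receipt is a secondary outcome, compared by log-binomial regression.

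The conclusions go further in three places:

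- **Abstract, Conclusions:** "This randomized trial will evaluate the preliminary efficacy of MI for targeting SARS-CoV-2 vaccine hesitancy". The same sentence then adds the comparison of traditional with app-based MI as a second item.
- **Discussion, Anticipated Findings:** the authors call it essential to study whether MI works for vaccine uptake in rural populations, say that this study meets that need, and mention a contribution on "the dose and intensity at which MI can be (cost-) effective".
- **Discussion, Conclusion:** "If MOTIVACC is found to be acceptable and effective, it could be an affordable and scalable stand-alone MI intervention".

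**The concern.** The stated aim and the randomised comparison do not match. The abstract treats the efficacy of MI as something the trial will deliver in addition to comparing modes, but nobody in the trial goes without MI. The only route from these data to a statement about MI itself is change from baseline within an arm, and randomisation does not protect that.

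What is at stake is the headline. If hesitancy falls in all three arms, or if some participants in each arm are vaccinated by week 8, the abstract's wording allows this to be reported as efficacy of MI. If MOTIVACC and SMI look alike, the same wording allows the app to be reported as working. Neither statement would follow from the design.

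**Working it through.** The point concerns structure, so the check is whether each effect can be estimated from the arms as described. The plan gives no figure to reproduce here.

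**Inputs.** The content of the three arms comes from the Procedure section and the contrasts from the Statistical Analysis section.

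**Step 1: write the arm means.** Let m be the mean outcome without MI, a the effect of the single session, b the effect of the three added sessions, and c the difference made by delivering MI through the app instead of the single session.

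- SMI = m + a
- IMI = m + a + b
- MOTIVACC = m + a + c

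**Step 2: count what the arms determine.** With columns (m, a, b, c), the rows are SMI (1, 1, 0, 0), IMI (1, 1, 1, 0) and MOTIVACC (1, 1, 0, 1). The first two columns are identical, so the matrix has rank 3 for 4 parameters.

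**Step 3: check each contrast.**

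| Contrast | In parameters | Estimable from the randomised arms? |
|---|---|---|
| IMI versus SMI | b | Yes |
| MOTIVACC versus SMI | c | Yes |
| Single-session MI versus no MI | a | No |
| IMI versus no MI | a + b | No |
| MOTIVACC versus no MI | a + c | No |

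**Step 4: show why.** Add any constant k to m and subtract k from a. All three arm means stay the same. The data therefore cannot separate a world in which MI works (a not zero) from one in which it does nothing (a = 0) and hesitancy has shifted by itself. More participants would estimate the arm means more precisely but would not separate m from a. In particular, c = 0 fits both the case where SMI and MOTIVACC work equally well and the case where neither works.

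**Step 5: consider within-arm change.** Change from baseline to week 8 in one arm is the effect of that arm plus time trend, the effect of being questioned twice, and regression to the mean. The last may be modest, because the eligibility criteria do not select on a hesitancy score. Vaccine receipt is more exposed: participants must enter without any dose, so receipt in an arm can only rise from zero, with or without an intervention effect.

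**Step 6: set this beside the text.** The contrasts in the Statistical Analysis section are b and c, and both are estimable. The efficacy of MI promised in the abstract and in Anticipated Findings needs a, a + b or a + c, and none of these is.

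**The case against.** The strongest reply is that this is a pilot comparing formats of MI, which is a legitimate aim for questions of dose and delivery. The text repeatedly says that efficacy is preliminary, and the Statistical Analysis section already words the contrast correctly and admits that power is insufficient for full hypothesis testing. All of that is true. It answers a complaint about precision. It does not supply a comparator, and the article nowhere acknowledges that one is missing.

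Part of the reply does stand and limits the point:

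- A reader might infer that the trial can say nothing about whether MOTIVACC is effective. That is too strong. A clear advantage over SMI would support MOTIVACC indirectly, provided that one session is not worse than nothing. IMI versus SMI is a randomised comparison of added sessions.
- A reader might infer that the article announces MOTIVACC will be shown to work. It does not: the sentence in the Discussion's Conclusion is conditional, and the one before it looks to later, fully powered trials.
- A reader might ask for an equivalence margin. The article makes no equivalence or non-inferiority claim, so none is needed.
- A reader might take low power as part of the error. The plan concedes it, and it is a separate matter.
- A reader might take the remark on cost as a promised economic analysis without data. The sentence offers only a contribution on dose and intensity. Contact completion is recorded in REDCap and in the app, and other measures may be in the full protocol, which is not shown.

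It may also be said that misreading is speculative, since no within-arm test of efficacy is planned. That is fair about the analysis. But the abstract's sentence claims the efficacy of MI as a result in its own right, and the planned analysis cannot provide it.

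**Conclusion.** The point holds as a mismatch between the stated conclusion and the randomised design. Randomisation gives no information on MI versus no MI at any sample size, so no number of participants, standard deviation or significance level enters the result. It rests only on the three arms being as the Procedure section describes them. The effects of added sessions and of app delivery, each relative to a single session, remain estimable, and the Statistical Analysis section describes them correctly. The error is in the abstract's Conclusions and in Anticipated Findings, with a lesser need for qualification in the Discussion's Conclusion. It should be corrected before results are reported, because it changes what the trial may conclude.

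**What to change.** By the Results section, recruitment of all 60 participants was complete by December 2024, so the remedy is to the text.

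1. **Abstract, Conclusions, and Discussion, Anticipated Findings:** say that the trial estimates, with 95% confidence intervals, the preliminary relative efficacy of IMI and of MOTIVACC versus a single MI session, and that it does not estimate the effect of MI versus no MI.
2. **Same places:** state that change within an arm, including vaccine receipt, is descriptive, and that a null MOTIVACC-SMI difference is not evidence that MOTIVACC works.
3. **Discussion, Conclusion:** qualify effective as more effective than single-session MI.
4. **Optional:** soften the reference to cost-effectiveness in Anticipated Findings.

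The Statistical Analysis section needs no change. The cost is a less favourable stated conclusion; no data collection or analysis is affected. A comparator without MI could be considered for the later, fully powered trial.

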**Trial Registration:**

ClinicalTrials.gov NCT05977192; https://clinicaltrials.gov/study/NCT05977192

**International Registered Report Identifier (IRRID):**

DERR1-10.2196/64010

## Introduction

Throughout the COVID-19 pandemic, rural populations have had lower rates of SARS-CoV-2 vaccination, increased vaccine hesitancy, and higher risks of morbidity and mortality associated with active infection than urban populations [1]. Increased likelihood of vaccine hesitancy has been associated with rural residence, low household income, and less education [2]. While some strides have been made in rural vaccination, it has been estimated that those who remain unvaccinated and currently reside in rural areas are less likely to consider vaccination (eg, will “definitely not” get vaccinated) [3]. In Oklahoma specifically, as of May 10, 2023, 68% of Oklahomans aged 18–35 years and 57% of Oklahomans aged 36-49 years had not received any dose of a SARS-CoV-2 vaccine [4]. However, in urban counties, 76%-95% of adults had received at least one dose, while the rates in rural counties ranged from 37%-65% [5]. Further, it has been estimated that as many as two-fifths of rural Oklahoman residents are hesitant to receive the vaccine [6].

Health communication has been consistently identified as a key element in promoting vaccine uptake and addressing vaccine hesitancy. Historically, approaches taken to communication vary [7] but may focus on attempts to craft persuasive informational messages [8]. The effect of these messages is likely minimized, as many individuals who are vaccine-hesitant perceive the source of information (eg, health care providers) as misinformed [8], thus a fundamental shift in the purpose of vaccine-related communication is essential. Such approaches may instead focus on honoring individual autonomy and navigating information and perceptions of information, versus relaying of information itself [9]. Data also suggest the advantage of using messages that emphasize the personal benefits of vaccination rather than prosocial benefits in reducing vaccine hesitancy; however, this may differ according to individual values [10]. Thus, it is critical to align individual priorities with intervention content, a key feature of motivational interviewing (MI) [11]. No studies have examined the effects of MI on vaccination rates among adults most vaccine-hesitant. MI has documented efficacy in vaccine-hesitant parents (eg, child HPV vaccines): vaccine intention rose by 12%, hesitancy decreased by 40% [12], and vaccine coverage in infants increased by 3.2%, 4.9%, and 7.3% at 3, 5, and 7 months of age, respectively [13]. MI has also been used to promote HPV vaccination in high-risk adults with promising results [14], but not necessarily in those who are vaccine-hesitant. While promising, MI delivery can be laborious, limiting scalability. Alternatively, mobile health (mHealth)–based interventions have been used to promote vaccination [15]. Thus, integrating MI into automated platforms is essential for scalability to improve public health.

The World Health Organization (WHO) acknowledges mHealth as a cost-effective, scalable, and sustainable way to improve public health [16]. A limiting factor in MI’s effectiveness is scalability due to the intensity of provider training and evaluation. Further, smartphone ownership in the United States increased from 35% in 2011 to 90% in 2023 [17] with similar rates across urban and rural groups (91% and 87%, respectively). Near-universal smartphone ownership provides an ideal yet untapped mechanism to deliver MI-based vaccine interventions to rural populations.

In summary, there is a critical need for improving SARS-CoV-2 vaccination rates among rural populations in Oklahoma and nationwide. To address this need, we will test the efficacy of an mHealth-based MI intervention to diminish SARS-CoV-2 vaccine hesitancy (MOTIVACC). This protocol paper aims to describe our mixed-methods approach to develop and pilot test the MOTIVACC. This study and subsequent course of research will contribute significantly to reducing vaccine-preventable morbidity and mortality in rural populations.

## Methods

### Study Design

This pilot study uses a mixed-methods, empathy-driven, user-centered intervention design strategy with two phases: (1) convening a community advisory panel (CAP) to understand emerging and current barriers and facilitators to vaccination and mHealth uptake among rural adults and (2) a pilot 3-group, 8-week-long randomized controlled trial (RCT) to examine the feasibility, acceptability, and preliminary efficacy of MOTIVACC. The CONSORT (Consolidated Standards of Reporting Trials) and SPIRIT (Standard Protocol Items: Recommendations for Interventional Trials) checklists were used.

### Conceptual Framework

Our study (particularly qualitative data analysis, MI interventions, and RCT measures) is guided by social cognitive theory (SCT), which posits that an individual’s cognition and health behavior change in a social context with dynamic and reciprocal interactions with other people and the environment [18]. Key constructs of SCT include expectations (eg, vaccination benefits or consequences of not being vaccinated), observational learning (eg, seeing the vaccine’s effectiveness), self-efficacy (eg, vaccine confidence), reciprocal determinism (eg, the dynamic and reciprocal interactions of the person with other people and the environment, that leads to vaccine acceptance, including eliminating stigma), reinforcements (ie, internal or external processes to vaccine acceptance or uptake), and behavioral capability (ie, the ability to obtain the vaccine through sufficient knowledge and skills) [19]. Interactions within the MI intervention will help to address reciprocal determinism and reinforcements, as it will entail direct interactions with personnel to address ambivalence toward vaccination, identify discrepancies between vaccination decisions and individual values, and provide information to participants in an empathetic and value-driven manner [11,19].

